### Recruitment {15}

Before randomization, investigators will screen potential hospitals through the national clinical research network. All eligible hospitals are first surveyed with a feasibility questionnaire to determine their willingness and capability to participate. Every eligible HF inpatient admitted to a study hospital is screened and invited to participate in the trial. The admission list and patient log from each participating site will be monitored to ensure sufficient consecutive HF patients are enrolled.

## Assignment of interventions: allocation

### Sequence generation, concealment, and implementation {16a,16b,16c}

Computer-generated random numbers are used to assign participating hospitals to the intervention or control group in a 1:1 ratio. Randomization is stratified by province to ensure the numbers of intervention and control hospitals are balanced.

Given the characteristic of the intervention, it will be impossible for the study investigator or the physicians to be blinded to the group allocation. The assignment of either intervention or control will be communicated to site investigators. However, the investigators at each site are blind to the sequence generation, thus ensuring that they have no opportunity to anticipate the allocation of their site until the study group assignment is revealed. In the second and the third influenza season, participating hospitals are re-randomized using the same process before the planned recruitment window.

## Assignment of interventions: blinding

### Who will be blinded {17a}

Given the nature of the study design, both study participants and site researchers will not be blinded. The data assessors and data analysts from coordinating center will be blind to the assignment of participants.

### Procedure for unblinding if needed {17b}

Not applicable.

## Data collection and management

### Plans for assessment and collection of outcomes {18a}

Data collection for both groups will be conducted concurrently and in parallel. Screening and baseline data will be collected and documented at the time of admission and during hospitalization by the pre-specified research team at each site. The population descriptive information, including demographics, anthropocentric, medical history, and concomitant medications, is collected by self-report. Results of laboratory test including blood, urine sampling, and echocardiogram will be retrieved. The electronic health records will be searched for source data validation, if available. Patients will be surveyed with quality of life and mood questionnaires: EQ-5D [19] and PHQ-9 [20]. Influenza vaccination data will be obtained prior to discharge. Centralized follow-up will be conducted by the coordinator center at each follow-up period to obtain information on deaths, re-hospitalization, occurrence of ILI, and any SAEs, along with the use of specific HF medications.

### Plans to promote participant retention and complete follow-up {18b}

Participants are required to provide four telephone numbers or contact details. If a participant is unable to complete a telephone follow-up, staff at the coordinator center will attempt to contact them through other available sources of information. If they are still unable to be assessed, their outcome or survival status will be confirmed through routine social network or health insurance systems, if available.

### Data management {19}

Data collection will be processed though customized web-based database. An electronic data capture system with range and logic checks will be used for both data entry and storage purposes. After the completion of data collection from various sources, the clinic coordinators will review each filled form for errors and completeness. As part of quality control measures, data reviews will be carried out to check consistency and logic issues on key variables. Data review reports will be generated and provided to sites and study committees on a regular basis to promote data quality.

### Confidentiality {27}

The research team has responsibility to ensure security and confidentiality of data at sites and the coordinating center. All individual and relevant site information will be de-identified before entry into the database and any statistical analysis to protect the privacy of all participants. Sources files or documents will be stored in locked filing cabinets at each site. Uploaded copies will be stored online in a non-URL accessible area that controlled by a system of user identification names and passwords encrypted with SSL encryption. Each site investigator must complete a data handling training program before they are given assess rights to the database. The study is conducted in compliance with Chinese national privacy and confidentiality laws.

### Plans for collection, laboratory evaluation, and storage of biological specimens for genetic or molecular analysis in this trial/future use {33}

No biological specimens will be involved in this study.

## Statistical methods

### Statistical methods for primary and secondary outcomes {20a}

#### General consideration

Continuous variables will be summarized by means (standard errors) and medians (inter-quartile intervals); if skewed, a transformation will be applied to induce approximate normality before testing. In any event that a suitable transformation cannot be found, a Wilcoxon test will be used. Descriptive statistics will be provided for patient characteristic, hospital characteristics, and safety data.

#### Endpoint analysis

The aim of the primary analysis will be to establish whether there are benefits in all-cause mortality or all-cause hospital readmission within 1 year (excluding events within 30 days post-discharge or occurring during a non-influenza season) from patients enrolled in the intervention hospitals compared with patients enrolled in the control hospitals. Aggregate cluster-level mean rates of primary endpoints between intervention clusters and control clusters will be compared by Wilcoxon rank-sum test. The intention-to-treat (ITT) principle will be applied.

In the secondary analysis, generalized linear mixed model will be performed to allow for the clustered nature of the data and to adjust the cluster-level covariates including province, hospital, and phase.

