### Trial design {8}

This is a two-arm, parallel group, cluster-randomized 1:1 controlled trial designed to determine whether a program of free influenza vaccination in hospitalized HF patients improves outcome compared to usual standard of routine care. The unit of randomization is the hospital where investigators are required to enroll consecutive patients with HF during a defined winter period. Hospitals are centrally randomly allocated to be an intervention arm to provide a free influenza vaccination in wards devoted to the care of patients with HF. The control hospitals are to provide usual standard of care without routine Point of Vaccination (POV) but can make recommendations to patients to receive their influenza vaccination at community health care center. This crossover may reduce the study’s ability to detect the vaccination’s effect. To account for this, we estimated that 10% in the control group would receive the vaccine and adjusted the sample size accordingly. The study was planned to be undertaken in phases over three years and for participating hospitals to be re-randomized before each winter recruitment period. A detailed flowchart is shown in Fig. 1.

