## Who will take informed consent? {26a}

### Consent process for hospitals

Sites are required to consent patients prior to undertaking any study procedures including randomization. The process of consent has the approval of the General Manager or Head of the Cardiology Department.

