### Consent process for individuals

Participants in the intervention arm provide consent for both vaccination and follow-up, whereas those in the control arm only provide consent for follow-up. Potential participants receive written information on the study and are given sufficient time to ask questions and make their decision. Refusal to participate does not influence the management of patients. Only patients with a signed informed consent are enrolled in the study. No study procedures or intervention will take place until the informed consent procedure is complete.

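### Unblinded staff recruit patients after the hospital's arm is known, but the stated adjustment covers cluster-level covariates only and cannot address patient-level imbalance

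*Protocol article*

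**What the plan says.** **Timing of allocation.** Trial design {8} plans "for participating hospitals to be re-randomized before each winter recruitment period". Sequence generation, concealment, and implementation {16a,16b,16c} says that in the second and third seasons "participating hospitals are re-randomized using the same process before the planned recruitment window". The same section adds: "The assignment of either intervention or control will be communicated to site investigators".

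**Blinding.** Who will be blinded {17a} states that "both study participants and site researchers will not be blinded". Only data assessors and analysts at the coordinating centre are blind.

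**Consent.** The section on individual consent sets out a difference by arm: "Participants in the intervention arm provide consent for both vaccination and follow-up, whereas those in the control arm only provide consent for follow-up".

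**Analysis.** Endpoint analysis gives the primary comparison: "Aggregate cluster-level mean rates of primary endpoints between intervention clusters and control clusters will be compared by Wilcoxon rank-sum test". No covariate enters it. The secondary analysis is a generalized linear mixed model that allows for clustering and is meant "to adjust the cluster-level covariates including province, hospital, and phase".

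**Safeguards.** Recruitment is to be consecutive up to the quota of 50 (Individual-level inclusion criteria). Patients who agree to follow-up are enrolled whether or not they want the vaccine (Intervention description {11a}), and refusers stay in the intention-to-treat analysis (section {11b}). Screening logs record the proportion of eligible patients who consent (section {11c}). Admission lists and patient logs are monitored (Recruitment {15}).

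**Baseline data.** Section {18a} lists demographics, medical history, medication, laboratory results and echocardiography. NYHA class III or IV is an entry criterion, and NYHA class is a planned subgroup factor (section {20b}).

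**The concern.** Randomising hospitals balances, in expectation, the hospitals and the populations they serve. It does not balance the patients who are enrolled if enrolment happens after staff and patients know the arm. Who is approached, and who agrees, can then depend on the arm. Here there is a visible route for this, because the consent discussion includes a vaccination offer in one arm and not in the other. The Background section itself gives cultural beliefs and safety concerns among the reasons for low uptake in China.

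The stated covariates do not reach this problem. Province and phase describe the place and the season. A hospital effect absorbs stable differences between hospitals. A change in patient mix that follows the arm within a hospital-season is left in the arm comparison. At stake is whether a modest difference in event rates can be read as an effect of the vaccination programme rather than of who was enrolled.

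**Working it through.** **1. Order of events.** Setting the sections side by side: hospital randomised before the window ({8}, {16}); arm communicated to the site ({16}); staff and patients unblinded ({17a}); patients screened and invited ({15}); consent taken, with different content by arm (Consent process for individuals). Patient recruitment follows known allocation.

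**2. The planned difference.** The article does not print it, so it is derived from Sample size {14}: infection 15%, endpoint risk if infected 80%, vaccine protection 60%, coverage 90% against 10%.

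0.15 × 0.80 × 0.60 × (0.90 − 0.10) = 0.0576, or 5.76 points (50.0% against 44.24%).

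This counts every endpoint event in an infected patient as caused by infection. A smaller attributable share would make the planned difference smaller and any given bias relatively larger.

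**3. The plan's own sample size.** With ICC 0.03, the design effect is 1 + (m − 1) × 0.03, and 122 hospitals give 61 per arm.

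- Three seasons pooled per hospital with 10% loss, m = 135: design effect 5.02, power 0.911. This is close to the stated 90%.
- Each hospital-season as its own cluster with 10% loss, m = 45: design effect 2.32, power 0.80.

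The present point does not depend on which reading is meant. Both are used in step 5 to bracket the standard error.

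**4. Size of a possible bias.** Bias in the event rate = imbalance between arms in the share of high-risk patients × risk difference between high-risk and other patients. Neither input is in the documents; both ranges are assumptions.

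| Imbalance (assumed) | Risk difference (assumed) | Bias | Share of 5.76 points |
|---|---|---|---|
| 5 points | 10 points | 0.05 × 0.10 = 0.5 points | 0.5 / 5.76 = 9% |
| 5 points | 20 points | 0.05 × 0.20 = 1.0 point | 1.0 / 5.76 = 17% |
| 10 points | 20 points | 0.10 × 0.20 = 2.0 points | 2.0 / 5.76 = 35% |
| 20 points | 30 points | 0.20 × 0.30 = 6.0 points | 6.0 / 5.76 = 104% |

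**5. Effect on the false-positive rate.** With no true effect, an event rate near 50% and a normal approximation, SE = √[2 × 0.25 × design effect / (61 × m)]. This gives 0.0206 for m = 45 and 0.0175 for m = 135. The two-sided error at nominal 5% is 1 − Φ(1.96 − b/SE) + Φ(−1.96 − b/SE) for a bias b.

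| Bias b | m = 45 | m = 135 |
|---|---|---|
| 1 point | 7.8% | 8.8% |
| 2 points | 16.3% | 20.9% |
| 3 points | 30.9% | 40.5% |

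These figures show how sensitive the comparison is. They are not an estimate of what happened.

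**The case against.** The strongest reply is that the protocol already guards against this. Entry requires consent to follow-up in both arms, and willingness to be vaccinated is not an entry condition, so the difference in consent content is not by itself an enrolment filter. Consecutive recruitment is checked against admission lists, and screening logs show how many eligible patients agree. This stands, and it lowers the risk. But consent to follow-up is still given after the arm is known and in a conversation that differs by arm. The stated use of the logs is feedback on adherence, not analysis.

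A second reply is that the analysis plan is not shown and may name patient-level covariates; the word 'including' leaves the list open. That is a fair limit on what can be claimed. A reader might infer that no planned analysis deals with the issue, and the document does not support going that far. It does, however, state the type of covariate as cluster-level, so the comment concerns what is written rather than silence.

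A third reply is that NYHA subgroups are planned, and estimates within NYHA class are not distorted by an imbalance in NYHA class. True, but this does not adjust the overall estimate and covers one factor only.

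Finally, frailty and vaccine hesitancy, which might drive selection, are not among the baseline variables listed. Covariate adjustment therefore cannot be presented as a full remedy.

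**Conclusion.** The point holds as a weakness in the stated analysis, not as a demonstrated bias. Recruitment follows known allocation, consent content differs by arm, and the described adjustment is confined to cluster-level factors in a secondary model, with none in the primary test. That adjustment cannot address patient-level imbalance arising after allocation.

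The size is unknown. Under the assumed ranges it runs from 0.5 to 6.0 points against a planned 5.76 points. The direction is also unknown. A reader might infer that the intervention arm would look healthier because frail or hesitant patients decline, but staff could equally steer sicker patients towards a free vaccine. The documents support neither.

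A reader might also take the sentence under Consent process for hospitals, "Sites are required to consent patients prior to undertaking any study procedures including randomization", to mean that patients consented before allocation. With hospitals randomised before each recruitment period, that order cannot apply to patients. The sentence sits under hospital consent and mentions approval by hospital management, so it looks like a slip of wording. It should be reconciled with {8} and {16}, but it does not change the analysis point.

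**What to change.** - **Secondary model.** Add pre-specified patient-level baseline covariates to the mixed model, for example age, sex, NYHA class and main comorbidities. Alternatively, keep the cluster-level test as it is and add a supportive two-stage analysis: regress the outcome on the patient covariates without arm, then compare the cluster-level residuals between arms.
- **Reporting.** Give the consent fraction by arm from the screening logs next to the baseline table by arm. This is the only direct evidence on selection through factors that were not measured.
- **Wording.** State that adjustment reduces bias from measured factors only. Reconcile the sentence on consent before randomisation under Consent process for hospitals with {8} and {16}.

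The cost is text in the analysis plan and some programming. Section {18a} and the entry criteria indicate that the variables are already collected, and the logs are already required. Enrolment closed on 8 February 2024, so recruitment cannot be changed, but analysis and reporting can. The covariate list should be fixed before anyone on the analysis side sees outcomes by arm; if that has already happened, the added analysis should be labelled post hoc.

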#### Interim analyses {21b}

No formal interim analysis will be conducted during the study. During the period of patient enrollment, interim analysis of major endpoints (including SAEs believed to be due to intervention) will be supplied by the independent trial statistician as soon as possible after the completion of patient follow-up during each influenza season, who will present these reports to the Chairman of the Data and Safety Monitoring Board (DSMB) along with any other analyses that the committee may request. The DSMB will advise the chairman of the steering committee if, in their view, the randomized comparisons in the trial have provided both (i) “proof beyond reasonable doubt” that one particular intervention is clearly indicated or clearly contraindicated in terms of a net difference in outcome and (ii) evidence that intervention expected to influence the patient management. Appropriate criteria of proof beyond reasonable doubt cannot be pre-specified precisely, but a difference of at least 3 standard deviations using the Haybittle-Peto stopping rule in an interim analysis of a major endpoint may be needed to justify halting or modifying the study prematurely. Site principal investigators (PIs) and study and steering committee personnel will remain blinded to the results of the interim analyses and safety assessments.

#### Methods for additional analyses {20b}

Subgroup analyses will be performed by province, year, and severity of HF (NYHA classification). For the degree of influenza activity, it is planned to classify influenza activity using the median ILI + /ILI of North and South China during the study period.

#### Methods in analysis to handle protocol non-adherence and any statistical methods to handle missing data {20c}

Consistent with an ITT analysis, this study will involve all participants in the primary analyses regardless of adherence. For participants lost to follow-up, all available information until the time of death or loss to follow-up will be used in analysis [21]. Missing values will be identified and replaced by a random sample of plausible values imputations (completed datasets).

## Oversight and monitoring

### Composition of the coordinating center and trial steering committee {5d}

The Heart Health Research Center (HHRC) in Beijing, China, coordinates the study and manages its daily operations. Responsibilities include center enrollment, ethics applications for each participating site, training local investigators to ensure high-quality trials, influenza vaccine procurement and distribution, data monitoring, and organizing meetings with the steering committee, DSMB, and investigators.

The steering committee, composed of trialists, cardiologists, and vaccine experts, is responsible for approving the study protocol and any amendments. The committee oversees the trial’s quality and progress and reviews DSMB reports to determine whether to continue or halt the trial.

This study plan to involve a comprehensive approach to data monitoring, combining central (remote) and on-site supervision. Prior to the initiation of the study at each participating site, all designated research personnel, including the PI, co-investigators, and research nurses/coordinators, receive comprehensive training on study procedures from the operational staff. Regular remote monitoring of data completion and quality is conducted throughout the study. Furthermore, the sponsor or their delegates will conduct annual visits to each participating center, in accordance with the study monitoring plan, to ensure adherence to the protocol, ICH-GCP guidelines, and relevant ethical and regulatory requirements. The monitor will meticulously verify participant informed consent and eligibility, and review relevant source documents, in accordance with a detailed monitoring plan. Upon completion of the study, the investigator is responsible to ensure the implementation of long-term storage plans for all relevant data and source documentation.

### Composition of the data monitoring committee, its role and reporting structure {21a}

An independent DSMB will conduct a comprehensive review of the study’s safety and outcomes every 6 months. The DSMB’s responsibilities encompass monitoring blinded response variables as well as SAEs to promptly identify any potential beneficial or detrimental effects for safety surveillance purposes. The DSMB will be governed by a charter that comprehensively delineates their responsibilities, procedures, and commitment to confidentiality. They will diligently furnish reports to the Central Coordinating Center (CCC) regarding recommendations on whether to continue or temporarily suspend recruitment for the study, based upon review of unblinded data from each influenza season’s conclusion. Additionally, they will monitor vaccination rate, influenza activity levels, vaccine strain compatibility with circulating strains, and attrition rates among participants as well as event occurrence frequencies. Safety reports will be made by the independent statistician after the occurrence of every 5 suspected unexpected serious adverse reaction (SUSAR) or after the occurrence of every 10 SAEs. Based on the outcomes of prior analyses, the DSMB may suggest to the steering committee a potential relaxation of these criteria.

### Adverse event reporting and harms {22}

The study vaccination’s safety will be assessed using a registry. Interim analyses on SAEs related to the intervention will be provided by an independent statistician to the DSMB Chair during each influenza season. If there is a significant difference (3 standard deviations) in a major endpoint based on Haybittle-Peto stopping rule, the study may be halted or modified. Adverse event following immunization (AEFI) will be reported to the steering committee and manufacturer’s pharmacovigilance team. SAEs must be reported to CCC within 24 h of the study team’s awareness, using the eCRF. Site investigators must also report SAEs to the relevant ethics committee within their specified timeframe.

All SAEs, whether related to influenza vaccine or not, must be evaluated for unexpectedness and vaccine association. Endpoints defined in the study will not be reported as adverse events. However, any other clinical signs and symptoms that are unexpected will be reported within 7 days post-vaccination.

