### Outcomes {12}

The primary outcome is the composite of all-cause death or all-cause hospitalization in influenza season (defined by national CDC) within 1 year after hospital discharge. Hospitalization is defined as clinical manifestations that require admission (for at least 24 h) or emergency room stay (for at least 24 h). Non-influenza season events are unlikely to be attributable to influenza infections. Events beyond the corresponding influenza season are unlikely to be prevented by influenza vaccine. Influenza vaccines are estimated to have protective effects by generating antibodies within 30 days post-vaccination, so events occurring within 30 days after discharge are considered unlikely to be preventable by influenza vaccination. Thus, events that occur in that occur in the non-influenza season or within 30 days after hospital discharge will be excluded from primary outcome analysis.

The secondary outcomes are:All-cause death within 1 year;All-cause hospital re-admission within one year;Composite of all-cause death or all-cause hospitalization within 6 months;All-cause death within 6 months;All-cause hospital re-admissions within 6 months.

Exploratory outcomes included the average number of all-cause hospital readmissions over a 1-year period, which refers to the average number of hospitalizations for any cause over a 1-year period. Another outcome is ILI, defined as ≥ 38 °C, cough or sore throat, within the past 7 days at each follow-up site. Safety outcomes are all-cause and cause specific serious adverse events (SAEs) according to standard definitions until the end of follow-up.

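### Study endpoints are exempt from adverse event reporting, but those endpoints are all-cause death and readmission, which contradicts the SAE safety outcome, the SAE evaluation rule and the 10-SAE report trigger

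*Protocol article*

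**What the plan says.** Three sections of the protocol article bear on this.

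- **Outcomes {12}.** "The primary outcome is the composite of all-cause death or all-cause hospitalization in influenza season", after excluding the first 30 days. The secondary outcomes include "All-cause death within 1 year;All-cause hospital re-admission within one year", with no season or 30-day exclusion stated. A hospitalisation is an event that "require admission (for at least 24 h) or emergency room stay (for at least 24 h"). The section then sets the safety outcome: "Safety outcomes are all-cause and cause specific serious adverse events (SAEs) according to standard definitions until the end of follow-up".
- **Adverse event reporting and harms {22}.** "SAEs must be reported to CCC within 24 h" of the study team becoming aware of them. "All SAEs, whether related to influenza vaccine or not, must be evaluated for unexpectedness and vaccine association". The next sentence is the exemption: "Endpoints defined in the study will not be reported as adverse events". The sentence after that asks for reports of other unexpected signs and symptoms in the week after vaccination.
- **Composition of the data monitoring committee {21a}.** The independent statistician makes a safety report after every 5 SUSARs "or after the occurrence of every 10 SAEs". The DSMB may suggest relaxing these criteria.

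**The concern.** Exempting endpoints from adverse event reporting is a recognised choice in trials with many events. It is safest when the endpoints are events of the underlying disease and suspected product-related cases are excepted. Here the endpoints are death and readmission from any cause, and no exception is stated. A death or admission caused by the vaccine is therefore itself an exempt endpoint.

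Three things are at stake:

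- the causality and unexpectedness assessment by which a SUSAR is recognised;
- the meaning of the all-cause SAE comparison between arms;
- the working of the 10-SAE trigger.

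A site faced with a readmission cannot obey both the rule to evaluate every SAE and the exemption. If sites resolve this differently, SAE counts by arm cannot be interpreted.

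**Working it through.** **Text check.** The article states no figure to reproduce, so the main check is to set the rules side by side.

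1. *What is exempt?* Any endpoint defined in the study. Because the 1-year secondary outcomes have no stated season or 30-day exclusion, this covers every death and every qualifying readmission or 24-hour emergency stay in the year after discharge.
2. *What is an SAE?* The article refers to standard definitions without listing them. I take these to be death, life-threatening events, hospitalisation or its prolongation, lasting disability, and other medically important events. Death and hospitalisation are the bulk of these in patients with NYHA class III or IV heart failure.
3. *What remains after the exemption?* Life-threatening, disabling or medically important events without a 24-hour stay, prolongation of the index admission, and non-fatal events between vaccination and discharge.
4. *Conclusion.* The safety outcome and the evaluation rule claim all SAEs, while the exemption removes most of them. No sentence says which prevails.

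**Scale of the trigger if endpoints count.** Inputs from Sample size {14}: 122 hospitals, 50 patients per hospital per season, and 50 events per 100 person-years after the season and 30-day exclusions.

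- Patients, reading 122 as hospital-seasons: 122 × 50 = 6,100. This fits Study setting {9}, which allows up to 60 hospitals a year.
- Proportion with an event, taking the rate as a proportion: 50%. Taking it as a constant hazard over one year: 1 − exp(−0.5) = 39%.
- Patients with an event: 6,100 × 0.50 = 3,050, or 6,100 × 0.393 ≈ 2,400.
- Ten-SAE reports: 3,050 / 10 = 305, or 2,400 / 10 = 240.
- From December 2021 (Trial status) to April 2025 (Participant timeline {13}) is 40 months: 305 / 40 = 7.6 a month, or 240 / 40 = 6.0 a month.

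These counts leave out repeat admissions, off-season events and the first 30 days, all of which add to them. Loss to follow-up and any vaccine benefit would reduce them. If 122 hospitals each recruited in all three seasons (122 × 50 × 3 = 18,300 patients), the 50% figure gives 915 reports.

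**The case against.** The strongest reply is that no event disappears. A reader might infer that early harm is hidden altogether, since events in the first 30 days are dropped from the primary outcome and endpoints are dropped from adverse event reports. The article does not support that. The secondary outcomes of death and readmission, at 6 months and at 1 year, keep days 0–30 and off-season events. If the exemption is read as covering only the primary outcome, early and off-season events are not exempt and are reported as SAEs. Neither reading loses them.

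Nor is the DSMB blind to deaths and admissions. Interim analyses {21b} supplies its chair with analyses of major endpoints after each season's follow-up. Section {21a} provides a review of safety and outcomes every 6 months and unblinded data at the end of each season.

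Other points also stand:

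- Some SAEs survive the exemption, so it would be wrong to say that the SAE outcome is emptied or near zero by construction.
- The trigger can be relaxed, so calling it unworkable goes too far.
- Adverse events following immunisation go separately to the steering committee and the manufacturer, although the article does not say whether the exemption overrides that route.
- The exemption speaks of adverse events rather than SAEs, and influenza-like illness is also a study outcome, so the sentence may have had milder events in mind.
- This is a condensed article, and an exception may sit in the full protocol. That weakens any point about a missing exception. It does not remove the contradiction between rules that are stated.

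**Conclusion.** The contradiction stands. As written, the exemption conflicts with the all-cause SAE outcome, with the rule that every SAE be reported within 24 hours and assessed, and with the 10-SAE trigger.

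Under the literal reading, a fatal or hospitalised suspected vaccine reaction need not be reported as an SAE or identified as a SUSAR. The by-arm SAE comparison omits most serious events, and the trigger has little to count. Under the other reading, the trigger fires roughly 240 to 305 times. That range rests on 6,100 patients and on 39% to 50% having an event, and it shows scale only; the finding does not depend on it.

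The loss is limited to case-level causality assessment and a coherent SAE outcome. Deaths and admissions remain visible by arm and to the DSMB, and the primary efficacy inference is unaffected.

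**What to change.** Reconcile Outcomes {12}, section {21a} and section {22}:

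- Limit the exemption to expedited reporting of individual cases, and exclude from it any event suspected to be vaccine-related. Such events then follow the 24-hour reporting and evaluation rules.
- State that all deaths and hospitalisations from vaccination or discharge, including days 0–30, enter the by-arm SAE tables and the DSMB reports. Control patients have no study vaccination day, so discharge is the natural common origin for the comparison; events between vaccination and discharge can be listed separately.
- State whether endpoint events count toward the 10-SAE trigger.

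The cost is modest. Central follow-up already collects deaths and rehospitalisations (Plans for assessment and collection of outcomes {18a}), so the tables need re-tabulation rather than new data. Enrolment closed in February 2024, so the reporting rule can change practice only for the remaining follow-up, but the tables can still cover every patient. Causality review is needed only for the few events suspected to be related. A full relatedness assessment of thousands of deaths and admissions would be a heavy load and is not proposed.
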